# Efficacy and safety of electroacupuncture treatment in the prevention of negative moods in healthy young men after 30 h of total sleep deprivation: study protocol for a single-center, single-blind, parallel-arm, randomized clinical trial

**DOI:** 10.1186/s13063-021-05659-x

**Published:** 2021-11-01

**Keywords:** Sleep deprivation, Electroacupuncture, Mood, Prevention, Randomized controlled trials

## Abstract

**Background:**

Sleep deprivation (SD) among young adults is a major public health concern. In humans, it has adverse effects on mood and results in serious health problems. Faced with SD, persons may take precautionary measures to try and reduce their risk. The aim of this study is to evaluate the efficacy and safety of electroacupuncture (EA) for the prevention of negative moods after SD. In addition, we will do a comparison of the effects of EA on mood after SD at different time points.

**Methods:**

This randomized controlled trial (RCT) will be performed at the First Affiliated Hospital of Changchun University of Chinese Medicine in China. The Standards for Reporting Interventions in Clinical Trials of Acupuncture 2010 will be strictly adhered to. Forty-two healthy male volunteers will be distributed into acupoints electroacupuncture (AE) group, non-acupoints electroacupuncture (NAE) control group, or blank control group. This trial will comprise 1-week baseline (baseline sleep), 1-week preventative treatment, 30-h total sleep deprivation (TSD), and 24-h after waking follow-up period. Participants in the AE group and the NAE control group during the preventative treatment period will be administered with EA treatment once daily for 1 week. Participants in the blank control group will not be administered with any treatment. The primary outcome will be the Profile of Mood States (POMS) Scale. Secondary outcome measures will include changes in the Noldus FaceReader (a tool for automatic analysis of facial expressions) and Positive and Negative Affect Schedule (PANAS) Scale. Total sleep deprivation will be 30 h. During the 30-h TSD period, participants will be subjected to 11 sessions of assessment. Adverse events will be recorded.

**Discussion:**

This study is designed to evaluate the efficacy and safety of EA for the prevention of negative moods after SD. The results of this trial will allow us to compare the effects of EA on mood after SD at different time points. Moreover, the findings from this trial will be published in peer-reviewed journals.

**Trial registration:**

Chinese Clinical Trial Registry Chi2000039713. Registered on 06 November 2020

## Administrative information

Note: the numbers in curly brackets in this protocol refer to SPIRIT checklist item numbers. The order of the items has been modified to group similar items (see http://www.equator-network.org/reporting-guidelines/spirit-2013-statement-defining-standard-protocol-items-for-clinical-trials/).

## Introduction

### Background and rationale {6a}

Sleep is an essential part of life. In modern societies, SD is particularly prevalent because many sacrifice sleep to meet work demands and social commitments. Clinically, SD is defined as “abnormal sleep that can be described in measures of deficient sleep quantity, structure, and/or sleep quality” [1]. It is characterized by sleep loss, restricted sleep duration, or REM sleep exclusion and is a major public health issue [2]. In recent years, the prevalence of SD in the society has been on the rise [3], thereby creating a challenge in the management of daily performance deficits due to sleep loss. SD endangers individual health, both in acute and chronic states. It has been documented that SD influences emotions [4] and can result in impairments in affective states (e.g., increased anxiety, depressed mood, anger, tension, frustration, and irritability) [5, 6]. Acute experimental SD has been associated with decreased social emotional functions, such as slower voluntary facial responsiveness to emotional stimuli [7], less accuracy in emotional face recognition [8], and an increased negativity bias [9]. These studies imply that SD impairs emotional information processing or causes such processing to be negatively biased. Epidemiological studies have shown that poor sleep is prospectively correlated with psychiatric morbidity, especially depression [10], where emotional dysfunction forms part of the symptomatology. In summary, there is evidence that the perception of emotional faces, as well as facial expressions, might be altered after SD.

The damage to human health that is a result of early SD is difficult to detect, and the modern medical testing equipment makes it difficult to accurately diagnose it before it causes significant organic damage to the body. However, SD has a significant negative impact on mood. Given SD can cause serious harm to the human body, it is important to seek reliable countermeasures and preventative measures in cases where it cannot be avoided or where the disease has already occurred. Currently, there are no official guidelines for the treatment of SD. The usual treatment for SD is to examine one’s sleep hygiene in order to eliminate behavioral habits that adversely affect sleep. However, due to increased work pressure and the fast pace of life in modern society, this self-treatment method is difficult to implement. Therefore, chemotherapeutic options should be considered. Currently, modafinil is the only FDA-approved medication for the treatment of sleep disorders in shift work [11]. Appropriately administered medications such as caffeine, modafinil, and amphetamines, which excite the center, can have an anti-sleepy fatigue effect. Although these drugs have been shown to be effective in clinical use, they have also been associated with many adverse effects, such as sleep interference, mental disorders, and addiction. Moreover, when used as sleep aids, some of these drugs can exacerbate daytime fatigue if the dose is too high or if the half-life is too long. Sedative sleep aids can also worsen SD [12].

Researchers and patients are seeking alternative options, such as non-drug therapies, for controlling negative emotions caused by SD. Acupuncture, as a typical treatment modality of traditional Chinese medicine (TCM), has been applied for diseases for over 2000 years. Acupuncture is a well-known form of Asian medical treatment that is used not only as an effective curative method, but also to prevent illness and maintain health. Electroacupuncture stimulation, an application of electrical current on acupuncture needles, is one of the most popular types of this traditional therapy. Studies have aimed at elucidating the underlying mechanisms of acupuncture. Recent meta-analyses have documented that EA can alleviate symptoms of insomnia, regulate related negative emotions, and improve the quality of life in patients with insomnia [13, 14]. Moreover, several studies have now shown that acupuncture can have a good regulatory effect on mood [15–17]. However, the preventive effect of EA on negative emotions after SD should be further verified in clinical trials. Therefore, we aim at performing a single-center randomized controlled trial to investigate the efficacy and safety of EA in the prevention of negative emotions after SD.

### Objectives {7}

This study is designed to evaluate the efficacy and safety of EA for the prevention of negative moods after SD. Moreover, the effects of EA on mood after SD at different time points will be compared. The findings of this trial will provide more reliable evidence for clinical acupuncture prevention in the treatment of negative moods after SD.

### Trial design {8}

This will be a single-center, single-blind, parallel-arm, randomized clinical trial. Forty-two healthy male volunteers will be allocated into the AE group, NAE group, or blank group with an allocation ratio of 1:1:1. This trial will comprise 1-week baseline (baseline sleep), 1-week preventative treatment, 30-h TSD, and 24-h after waking follow-up periods. Figure 1 shows the flow diagram of the trial.

**Fig. 1 Fig1:**
[figure not shown]
Flow diagram of the trial

## Methods: participants, interventions, and outcomes

### Study setting {9}

This RCT will be performed at the First Affiliated Hospital of Changchun University of Chinese Medicine, China. It is a comprehensive tertiary level Chinese medicine hospital with medical treatment, scientific research, prevention, and health care. The hospital has a clinical research center for acupuncture and moxibustion. This study will be conducted in accordance with the Declaration of Helsinki and has been approved by the Ethics Committee of the First Affiliated Hospital of Changchun University of Chinese Medicine (CCZYFYLL2020-054) and has been registered in the Chinese Clinical Trial Registry (ChiCTR2000039713).

### Eligibility criteria {10}

All participants will be subjected to a standardized interview and be given more information about this study. To minimize treatment bias, the acupuncturists who will be involved in this trial are specialists in acupuncture, with more than 5 years of experience in acupuncture treatment. They have valid acupuncture licenses (Chinese medicine practitioner license) from the Ministry of Health of the People’s Republic of China. Before performing this trial, the acupuncturists will receive special training regarding the purpose and content of the trial, treatment strategies, and quality control. In this study, we selected non-smoking men as the study subjects for this trial. Evidence indicates that women are more susceptible to the maladaptive emotional consequences of SD than men [18, 19]. The prevalence rates for both insomnia and anxiety disorders are higher in women relative to men [20, 21]. Women also demonstrate a stronger comorbidity of sleep disturbance and anxiety disorders than men [22]. However, there were also gender differences in the response to electroacupuncture treatment in subjects. In addition, nicotine consumption through tobacco products is highly comorbid with mood disorders, including depression, anxiety, and irritability. Tobacco use could precipitate mood dysregulation [23]. However, many studies have reported that nicotine can improve symptoms of depression under some conditions [24, 25]. This study is designed to evaluate the efficacy and safety of electroacupuncture treatment for the prevention of negative moods in healthy young men after SD. Therefore, we chose non-smoking males as the subjects for this trial.

### Inclusion criteria

The inclusion criteria will be as follows:
iHealthy male volunteers aged 18 to 30 years at the screening visit.iiParticipants must not have had any congenital defects or chronic diseases within the 3 years prior to the screening visit and should have no pathological or abnormal clinical findings on physical examination.iiiParticipants must not have any sleep disorders and must have Pittsburgh Sleep Quality Index (PSQI) scores of 7 points or lower.ivParticipants must have Self-rating Anxiety Scale (SAS) scores of 50 points or lower and Self-rating Depression Scale (SDS) scores of 53 points or lower.vParticipants must keep normal nocturnal sleeping hours (between 21:00 and 09:00) for a week before the first clinical trials.viParticipants must sleep for at least 7 h per night for a week before the first clinical trials.viiParticipants must be non-smokers or ex-smokers who stopped smoking at least 1 year before the screening visit.viiiAn agreement to participate in the study by signing the informed consent.

### Exclusion criteria

Participants who experience, have, or have had one or more of the following will be excluded:
iHistory of regular alcohol consumption (> 210 g/week) within the 6 months before the screening visit (beer (5% v/v): 250 mL = 10 g, soju (20% v/v): 50 mL = 8 g, wine (12% v/v): 125 mL = 12 g)iiParticipation in another clinical study within 2 months before the screening visitiiiIntake of prescribed or over-the-counter drugs within 7 days before the first clinical trialsivParticipants who will have received acupuncture treatment during the 7 days before the first clinical trialsvParticipants with a fear of acupuncture or infection related to the locations of Baihui (GV-20), Shenmen (HT-7), and Sanyinjiao (SP-6)

### Who will take informed consent? {26a}

Personal information will be collected after oral and written consents are obtained from each participant at the first visit. After potential participants voluntarily consent to the study, they will be screened using pre-determined inclusion/exclusion criteria at the first visit. Written informed consent will be obtained from all the participants by the principal investigator or sub-investigators prior to enrollment.

### Additional consent provisions for collection and use of participant data and biological specimens {26b}

This will not be applicable as no biological specimens will be collected for research purposes.

### Interventions

The two control interventions will be NAE and the blank control. The manipulation of NAE will be conducted as described below. To eliminate out placebo effects, the NAE control group will be used. The blank control group will be used to assess whether EA is effective. Intergroup comparisons will be done for the three groups.

#### Intervention description {11a}

Interventions will be according to the records in ancient books and research results of modern papers about treating diseases related to sleep disorders with acupuncture in China or in the West [26–29]. These interventions will be slightly modified by Chinese acupuncturists and acupuncture experts from the study team and non-study team in all regions where the study will be conducted. The project team has made SOPs for clinical research to ensure that the treatment is followed throughout the clinical research. Participants will be randomly allocated into one of three groups: the AE group, the NAE control group, or the blank control group.

#### The acupoints electroacupuncture group

The acupoints to be used in the AE group are Baihui (GV-20), Shenmen (HT-7), and Sanyinjiao (SP-6), which are recommended points for the treatment of diseases related to sleep disorders [30, 31]. HT-7 is the point with the highest frequency of use [32], and SP-6 and GV-20 are often used with HT-7 as a combination regimen according to the TCM theory and clinical experience of acupuncture therapists [33]. The acupuncture operation is based on the textbook of the 13th Five-Year Plan of the Ministry of Health. Participants will be required to take the supine position. Acupoints will be needled after disinfection. Baihui (GV-20) will be horizontally punctured 0.3–0.5 cun (the acupuncture needle tip travels in the opposite direction to the meridian circulation of Dumai meridians). Shenmen (HT-7) will be perpendicularly punctured 0.5–0.8 cun while Sanyinjiao (SP-6) will be perpendicularly punctured 1.0–1.5 cun. All acupoints will be localized according to the WHO Standard Acupuncture Locations as shown in Table 1 and Fig. 2.

**Table 1 Tab1:** Locations of acupoints for the acupoint EA and non-acupoint EA groups

Group	Acupoint	Location	Descriptions
1	Baihui (GV-20)	At the vertex on the midline, in the depression 5 cun posterior to the anterior hairline and 7 cun superior to the posterior hairline	Punctured horizontally 0.3–0.5 cun
	Shenmen (HT-7)	At the wrist joint, on the radial side of flexor carpi ulnaris, in the depression at the proximal border of the pisiform bone	Punctured perpendicularly 0.5–0.8 cun
	Sanyinjiao (SP-6)	On the medial side of the lower leg, 3 cun superior to the prominence of the medial malleolus, in a depression close to the medial crest of the tibia	Punctured perpendicularly 1.0–1.5 cun
2	Non-acupoint 1	On the edge of the tibia 1 to 2 cm lateral to the Zusanli (ST36) horizontally	Punctured perpendicularly 0.5–1 cun
	Non-acupoint 2	On the half between the tip of the elbow and the axilla	Punctured perpendicularly 0.5–1 cun
	Non-acupoint 3	On the ulnar side, half between the epicondylus medialis of the humerus and the ulnar side of the wrist	Punctured perpendicularly 0.5–1 cun

Group 1: acupoints electroacupuncture group

Group 2: non-acupoints electroacupuncture control group

^a^1 cun (≈ 20 mm) is defined as the width of the interphalangeal joint of the patient’s thumb

**Fig. 2 Fig2:**
[figure not shown]
All acupoints

#### Non-acupoint electroacupuncture control group

In the NAE control group, we will select non-acupoints as reported in previous studies, including non-acupoint 1, non-acupoint 2, and non-acupoint 3. Non-acupoint 1, the edge of the tibia 1 to 2 cm lateral to the Zusanli (ST-36) horizontally [34], will be perpendicularly punctured 0.5–1 cun. Non-acupoint 2, half between the tip of the elbow and the axilla [35], will be perpendicularly punctured 0.5–1 cun. Non-acupoint 3, the ulnar side, half between the epicondylus medialis of the humerus and the ulnar side of the wrist [35], will be perpendicularly punctured 0.5–1 cun. All non-acupoints are shown in Table 1 and Fig. 2.

In each session, all acupoints and non-acupoints will be bilaterally punctured by filiform needles. After the puncture of 3 acupoints or non-acupoints by needles, 6 auxiliary needles will be punctured at 2 mm lateral to every acupoint or non-acupoint and punctured to a depth of 2 mm without manual stimulation. Transcutaneous electric acupoint stimulation (Hwato SDZ-V Acupoint Nerve Stimulator, Suzhou Medical Co., Ltd.) will be used for electro-acupuncture stimulation at every acupoint or non-acupoint after needle insertion. Each acupuncture needle at the acupoints or non-acupoints and auxiliary needles will be connected to the electricity by Hwato SDZ-V for 30 min. The stimulation frequency will be 2/100 Hz. The stimulation intensity will vary from 0.1 to 1.0 mA until the patients feel comfortable. The Massachusetts General Hospital Acupuncture Sensation Scales (MASS) will be used to determine whether the De-Qi sensations are produced during acupuncture. To screen for patients with the De-Qi sensation. The intensity of soreness, numbness, heaviness, warmth, cold, sharp pain, and dull pain will be rated on a numerical scale of 1–10.

The filiform needles to be used in this trial are single-use sterile acupuncture needles, namely Hwato Needles, made in Suzhou, China, 25–40 mm in length and 0.25 mm in diameter. Needles with a length of 13 mm and a diameter of 0.18 mm will be used as auxiliary needles without manipulation. De-Qi sensation will be achieved in the acupoints of the AE group by lifting and thrusting combined with twirling and rotating the needles. However, De-Qi sensation will not be achieved in the non-acupoints of the control group by the same needle manipulation methods. Needles will be retained in the AE group and the NAE control group for 30 min; afterwhich, the acupoint holes will be closed using clean cotton balls to avoid bleeding when withdrawing the needle. Participants in the two groups will be administered with 7 treatments over a period of 1 week, once a day.

#### Blank control group

Participants in the blank control group will not be given any treatment.

### Sleep deprivation procedures

The SD trial will be performed at the Clinical Centre for Acupuncture and Moxibustion at the First Affiliated Hospital of Changchun University of Chinese Medicine, China. Sleep deprivation will start at 7:00 am (baseline). Total sleep deprivation will be 30 h. During their free time, participants will spend most of their time in a large common room with both natural and electric lighting. During SD, participants will be permitted to play games, read, review school work, and use their personal electronic devices for entertainment. They will also be allowed to freely interact with each other and with the research staff. Napping, caffeinated beverages, and strenuous physical activity will be prohibited. Participants will be served breakfast, lunch, and dinner in the hospital cafeteria, with free access to snacks during their free time in the common room. Throughout the trial, participants will be constantly supervised by the researcher to ensure they do not fall asleep.

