### Outcomes {12}

#### Primary outcome

##### Profile of Mood States Scale

The POMS [36] is a well-validated, 65-item self-report measure comprising six subscales: tension/anxiety, depression/dejection, anger/hostility, energy/activity, fatigue/vigor, and confusion/bewilderment. Participants will report on their mood using a 5-point scale (“not at all” to “extremely”).

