### Assignment of interventions: blinding

#### Who will be blinded {17a}

Blinding methods will be applied to data statisticians and outcome evaluators throughout the trial. They will not be able to obtain information regarding the grouping and treatment of participants. Acupuncturists will not be masked due to the nature of acupuncture. However, acupuncturists will not participate in the data collection, statistics, and final outcome evaluation. For the intervention, different volunteers will be assigned to different treatment rooms with independent beds so as to avoid contact among subjects. Personnel in charge of random grouping, acupuncture treatment, data processing, and outcome evaluation will be completely separated so as to ensure the authenticity of the outcome of the trial to the greatest possible extent.

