### Data collection and management

#### Plans for assessment and collection of outcomes {18a}

Prior to the start of the trial, all data assessors will be uniformly trained in order to improve the quality of the data assessment. The primary outcome measure will be obtained using POMS while the secondary outcome measures will be obtained using PANAS and FaceReader. These three instruments have been widely used in trials related to the detection of mood changes [36–38]. During the 30-h TSD period, participants will be assessed every 3 h for a total of 11 assessments. During the 24-h after waking follow-up period, participants will also be assessed once.

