This study has some limitations. First, the design is a single-blind trial. When participants sign the informed consent form, they are informed that this study is aimed at elucidating the efficacy of three interventions, and participants will be randomly assigned to any one of the groups. Due to the nature of acupuncture, masking acupuncturists is quite difficult. Therefore, 3 groups of participants will be allocated in different treatment rooms, and each participant will be separately treated to avoid communication between the participants in the group. Second, this is a single-center trial in China, and whether the results will have generalized significance for other subjects is unknown. The study has some limitations in terms of the selection of subjects. Studies [43, 44] have shown that older people are less emotionally affected by SD than younger people and that the negative effects of SD are stronger in younger people than in older people. Moreover, the effects are greater among women than in men. Therefore, in order to exclude age and gender effects, only healthy adult males (18–30 years) will be selected for our study. At the end of this trial, we hope that the results will provide more reliable evidence for clinical acupuncture prevention in the treatment of negative moods after SD.

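### Participants are kept apart during needling to prevent contact, but may mix freely during the 30-h sleep deprivation when the self-rated primary outcome is collected, which can compromise the AE–NAE masking

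*Protocol article*

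**What the plan says.** Two places in the protocol article use physical separation to protect masking. The section Who will be blinded {17a} says that, for the intervention, "different volunteers will be assigned to different treatment rooms with independent beds so as to avoid contact among subjects". The Discussion, on the limitation that the trial is single-blind, again puts the groups in different rooms, where "each participant will be separately treated to avoid communication between the participants in the group".

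The section Sleep deprivation procedures sets different conditions for the next phase. During their free time "participants will spend most of their time in a large common room", and "They will also be allowed to freely interact with each other and with the research staff". It mentions neither separation by arm nor a limit on what may be discussed.

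The outcome is collected in that phase. Plans for assessment and collection of outcomes {18a} states: "During the 30-h TSD period, participants will be assessed every 3 h for a total of 11 assessments". The primary outcome, POMS, is a "65-item self-report measure comprising six subscales", and PANAS is also rated by the participant. On who is masked, section {17a} says: "Blinding methods will be applied to data statisticians and outcome evaluators throughout the trial". The Interventions section gives the NAE arm the task of removing placebo effects.

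**The concern.** For a self-rated scale the participant is the assessor, so masking evaluators and statisticians does not protect the score. What protects the AE–NAE comparison is that needled participants do not know which kind of needling they had. The separate rooms serve that purpose until treatment ends, but the purpose lasts until the last POMS is completed, and the separation stops before the in-deprivation assessments.

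If AE and NAE participants work out their allocation during TSD, a difference between them on POMS can no longer be read as the effect of the acupoints with expectation removed. Staff who hear the same conversations could also pass allocation on to the evaluators, whom section {17a} wants kept unaware. The Discussion names imperfect blinding in earlier acupuncture studies as something this trial means to overcome, so the gap touches a stated aim.

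**Working it through.** The main point rests on setting the sections side by side. The plan gives no figure for it to reproduce.

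**1. Overlap in time.** TSD starts at 7:00 am and lasts 30 h. Assessments every 3 h give 30/3 + 1 = 11, which agrees with Participant timeline {13} (7:00 am to 13:00 the next day). The first is at the start of TSD. The other 11 − 1 = 10 come after at least 3 h in which contact is allowed.

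**2. What conversation could reveal.**
- Needle sites (Table 1): AE uses the top of the head, the wrist and the inner lower leg. NAE uses the shin, the upper arm and the forearm.
- Sensation: De-Qi is sought in AE and is not to be reached in NAE. Sensations are rated with the MASS scale.
- Existence of the alternatives: the Discussion says participants learn at consent that three interventions are compared.
- Blank arm: no treatment, so these participants know their allocation whatever the room arrangement.

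What free contact can add is therefore mainly AE–NAE unmasking and disclosure to staff. The section on TSD does not say whether the supervising staff are separate from the outcome evaluators.

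**3. Secondary check: shared sessions and the ANOVA.** Statistical methods {20a} compares the three groups by one-way ANOVA at each time point, which treats participants as independent. People in one session may share mood. The documents give no session size, no session composition and no intraclass correlation (ICC), so the following is illustration under assumptions. The trial has 42/3 = 14 participants per arm. Assume sessions of m = 7 and an ICC of 0.05, 0.10 or 0.20.

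If every session held one arm only, the variance of an arm mean would be multiplied by 1 + (m − 1) × ICC:
- 1 + 6 × 0.05 = 1.30
- 1 + 6 × 0.10 = 1.60
- 1 + 6 × 0.20 = 2.20

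Simulated type I error of the one-way ANOVA at nominal 5% (10,000 trials per cell for the first two rows; 40,000 trials for the last):

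| Session make-up (assumed) | ICC 0.05 | ICC 0.10 | ICC 0.20 |
|---|---|---|---|
| One arm per session, sessions of 7 | 10.1% | 16.0% | 27.7% |
| Sessions of 7 formed independently of arm | 5.1% | 4.9% | 4.9% |
| Two sessions of 21, arms balanced (7 each) | not run | 4.3% | 3.9% |

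Over session sizes 6 to 14 and the same ICCs, arm-specific sessions give 8% to 49%, and sessions formed independently of arm give 4.6% to 5.4%. In the balanced layout the session effect cancels between arms but stays in the error term. The test is then slightly conservative, and a session factor would recover that precision.

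**The case against.** The strongest reply is that there is no literal contradiction. The separate rooms are prescribed for the intervention, the common room for a later phase, and a 30-h supervised vigil is hard to run in isolation. Section {17a} also lists only statisticians and evaluators as masked, the Discussion concedes the single-blind design, and comparing sites does not by itself tell a lay participant which sites are genuine. House rules on conversation may exist in the SOPs that the article mentions.

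Part of this stands. Free contact cannot be said to defeat the masking: the article does not list participants among those masked, the blank arm was never maskable, and the common room covers most free time, not every minute. What does not fall away is the purpose. The article gives avoiding contact and communication as the reason for separation, then expressly permits contact when the self-rated outcome is taken. That is a conflict in stated text, not a missing detail. The placebo role given to NAE also presupposes that participants cannot tell the two needled arms apart.

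Two stronger readings are tempting. A reader might infer that the bias favours AE over blank. The documents do not show this: blank participants know their status before TSD, and shared mood in a mixed room could pull the arms together. A reader might also infer that shared mood raises the ANOVA's false-positive rate to 10–28%. That needs arm-specific sessions, which no section states, and the article allocates individuals at random. The two harms also largely exclude each other: AE–NAE comparison in the room needs the arms together, while the inflation needs them apart.

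**Conclusion.** The point holds in limited form. Sleep deprivation procedures undercuts the safeguard in Who will be blinded {17a} and the Discussion. If the arms share the common room, AE–NAE masking can be compromised for ten of the eleven in-deprivation POMS and PANAS assessments, and staff can learn allocation. This rests on three assumptions: arms are present together, participants talk about treatment, and no unpublished rule prevents it. The documents give no basis for a size or direction of bias.

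Non-independence within sessions is secondary. With sessions formed independently of arm, type I error stays near 5%. The inflated figures are illustrative only.

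**What to change.** Reconcile the three sections by extending the no-communication rule to TSD:
- Tell participants not to discuss needling, sensations or allocation with each other or with staff.
- Keep supervising staff unaware of allocation and tell them not to ask.

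This costs an instruction sheet, some staff scheduling and slightly stricter house rules. The common room can stay.

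Secondary: form TSD sessions with the three arms mixed, record each participant's session and, if there is more than one, include session as a factor in the model. This costs some scheduling and one model term. Mixing makes conversation across arms possible, so it should go together with the rule above.

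Trial status puts the end of recruitment at 20 May 2021. If the TSD sessions have already been run, report the unrestricted contact as a limitation of the AE–NAE comparison, and model session where it was recorded.
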